### Screening and study initiation

This study will identify those patients who present to the ED and require mechanical ventilation. Each site has a system in place for real-time alerts (24 h/day) when mechanical ventilation is used in the ED, and has validated its notification system from the ED to ensure the population of potentially eligible patients will be consecutive mechanically ventilated patients presenting to the ED. All patients that satisfy inclusion and exclusion criteria will be enrolled.

### Interventions

Patients in the control phase of the trial will receive usual, clinician-directed care. To limit a Hawthorne-like effect, clinicians will have no knowledge of the study during the control. After 6 months, as determined by computer-generated randomization, a site will enter a 2-month transition phase, during which we will implement a multifaceted intervention aimed at reducing the use of rocuronium in the ED and consequently increase the use of succinylcholine. The intervention will be delivered at the cluster level, and the strategies employed revolve around the use of “nudges” without restricting clinician choice [50]. Nudges can be a powerful strategy to modify clinician behavior in order to increase uptake of evidence-based practices [48, 50–52]. A type of nudge involves the use of “defaults”; default options are those set in place when no alternatives are actively chosen and they have been shown to positively influence clinician decisions [50]. Succinylcholine will be the default NMB over rocuronium because (1) it has been the default NMB of choice in the ED for > 40 years [53]; (2) its 5-min duration of action greatly reduces AWP risk; (3) our preliminary data regarding AWP and its association with rocuronium [19, 23]; (4) ED rocuronium use has increased despite no patient-centered studies showing benefit over succinylcholine [17, 21]; and (5) a robust body of literature which documents equivalent efficacy and safety profiles of succinylcholine and rocuronium [54–56].

A basic challenge of pragmatic clinical trials is to design an intervention that is appropriately balanced with respect to flexibility (i.e., it must be adaptable to local culture) and adherence (i.e., it must cause some level of change in order for efficacy to be adequately tested). In addition, a fundamental aspect of nudges is their influence on decisions without restricting choice. Due to these issues, our multifaceted intervention strategy will have both mandatory (standardized) and optional interventions during the transition phase. For the mandatory interventions, we will educate and engage (1) with emergency medicine (EM) physician and nursing leadership to secure endorsement of the trial; and (2) to deliver standardized presentations and lectures to clinicians and trainees (e.g., grand rounds, faculty meetings). We will also use passive alerts in the form of (1) strategically placed laminated graphics which advertise and promote the trial in the ED; and (2) distribution of a one-page document, which contains the background, rationale, and goals of the trial in one convenient location. Finally, active alerts will include (1) announcement of succinylcholine as the default NMB in the nursing “huddle” (before shifts); and (2) monthly emails to clinicians showing the breakdown of NMB use (continuous quality improvement). Optional interventions will be dictated by local culture and resources, or as needed if intervention fidelity declines over time. These include the use of ED-based pharmacy resources to advertise and promote the trial, as well as modification of access to rocuronium, making succinylcholine a more “convenient” option to clinicians (e.g., in the bedside airway box versus the automated medication dispensing system). If needed, we will identify more local champions, in addition to each site principal investigator, to participate in and promote the trial. Finally, if needed we will send emails to individual clinicians each time rocuronium is used in order to explore the rationale for its choice. This provides *accountable justification* regarding NMB choice (i.e., justification of the decision to not use the default). After the 2-month transition phase, each site will begin the intervention phase, in which enrollment will be resumed.

We will aim to prevent drift of intervention fidelity over time in several ways. Sites with an earlier transition to the intervention will be able to advise subsequent sites on troubleshooting, potential pitfalls, and successes. In addition, the active alerts (see above) will provide routine reminders to the clinical staff regarding the trial. We will also monitor the breakdown of NMB use on a rolling and near-continuous basis and present these results at our ED-AWARENESS-2 team meetings. If problems with treatment fidelity are observed, we will re-educate clinical staff at the site and tailor the intervention re-education as needed. In addition, we will more uniformly employ the optional interventions in order to increase intervention fidelity. In this way, we not only have uniform and mandatory interventions to be employed at the onset of the trial at each site, but also maintain optional interventions which can be strategically “in our back pocket” if needed.

### Informed consent

We will conduct the study with waiver of the requirement to obtain signed informed consent. The control phase is entirely observational. The intervention uses nudges and defaults for quality improvement, according to guidelines and recommendations regarding AWP prevention. In addition, for continued monitoring and quality improvement, the assessment of AWP is part of standard routine post-intubation care for millions of mechanically ventilated patients undergoing anesthesia annually in the USA, and it is also part of ongoing quality improvement initiatives in mechanically ventilated ED patients. However, all care will remain at the discretion of treating clinicians, and data during the intervention phase will also be collected under observational conditions. Specifically, while our intervention is aimed at reducing the use of rocuronium in the ED in order to prevent AWP, the final choice of all treatment decisions will remain at the discretion of the treating clinical team at all times. The only processes for research are administration of the mental health and quality of life questionnaires, at days 30 and 180, and medical record review. Verbal informed consent will be obtained prior to administration of the day-30 and day-180 follow-up questionnaires.

Washington University in St. Louis will act as the single institutional review board for this trial. The study protocol has received ethical approval (Additional File 1) by the Human Research Protection Office at Washington University School of Medicine in St. Louis (IRB # 202207132).

### Outcome measures

The primary outcome is the proportion of patients experiencing AWP in the control phase versus the intervention phase. Our methodology to assess for AWP is congruent with large operating room trials, and our prior approach [19, 20, 57, 58]. The modified Brice questionnaire has been used for > 50 years to assess for AWP and will be used in this trial (Additional File 2) [59]. To be considered for AWP, patients must report memory of paralysis either before (i.e., recall of intubation) or after (i.e., waking with paralysis) losing consciousness [19]. Because of simplicity and excellent diagnostic accuracy, the Richmond Agitation-Sedation Scale (RASS) will be used to screen for delirium and before assessment of AWP [60]. AWP will be assessed at one time point. Trained team members who will check the medical record daily for extubation and assess for AWP before hospital discharge, under waiver of the requirement to obtain signed informed consent. In patients discharged during off hours (e.g., weekends, night), we will assess AWP via telephone. The final determination of AWP will be independently adjudicated by three experts who will be provided questionnaire responses, qualitative reports of patient experience, and pertinent clinical data. Reviewers will adjudicate events as no, possible, or definite AWP, and determined when ≥ two agree. If all hold opposing views, a fourth reviewer will assist. Reviewers will be blinded to NMB, sedation medications, and trial phase.

Secondary outcomes include mental health and quality of life assessments at 30 and 180 days after hospital discharge, assessed via telephone follow-up after obtaining verbal informed consent. Questions will be asked in reference to the index hospitalization. PTSD symptoms will be measured using the PTSD Checklist for DSM-5 (PCL-5), a validated 20-item (score 0–4, Likert scale) self-reported measure that assesses 20 DSM-5 symptoms of PTSD (clinically significant symptoms = PCL-5 > 32) [61]. While PTSD is our main secondary outcome of concern, depression, anxiety, and impaired quality of life (QOL): (1) often co-exist with PTSD; (2) are common after critical illness; and (3) are also sequela linked to AWP [1, 2, 5, 7, 10, 25, 62, 63]. To give a broad picture of burden endured by survivors, we will assess for depression and anxiety with the Hospital Anxiety and Depression Scale (HADS), a validated 14-item (7 depression, 7 anxiety, ordinal score 0–3) questionnaire commonly used in critical illness [25]. We will evaluate QOL with EuroQol-5D (EQ-5D), the most widely used scale for measuring health-related QOL and part of the core sets recommended for critical care studies on post-discharge outcomes [64, 65].

To assess for potentially modifiable intervention targets for future trials aimed at PTSD symptom prevention, we will collect patient perception of (1) perceived threat; (2) clinician compassion; and (3) degree of family/friend emotional support. Perceived threat will be measured with the validated 7-item tool used in our prior work [19, 38, 66, 67]. Patient perception of clinician compassion will be assessed with a 5-item measure, developed, and validated by our team (only instrument validated for ED use) [68]. Family/friend emotional support during hospitalization will be assessed with two items previously used in the ED as measures of anxiety-provoking social support that are significantly associated with PTSD symptoms: (1) “How much of the time did your support person need you to comfort them?”; and (2) “How much of the time did your support person make you anxious?” [69].

### Data

Patient-level data will be easily accessible from the electronic medical record. The following baseline characteristics will be collected: age, gender, race, weight, height, pre-existing comorbid conditions, vital signs at presentation, and pertinent laboratory variables. Pre-intubation mental status, drugs used to facilitate intubation, and ventilator settings in the ED will be collected. After the initiation of mechanical ventilation in the ED, all medications related to analgesia and sedation in the ED will be collected. Sedation depth in the ED will be recorded by bedside nurses, using validated sedation depth scales, such as RASS or the sedation-agitation scale (SAS), per existing protocols [70].

The following in-hospital data will be collected: duration of ventilation, agents used for analgesia and sedation during the first 24 h of ICU admission, depth of sedation during the first 7 days after admission, lengths of stay in the ICU and hospital, discharge location, and mortality status (Table 1).

**Table 1 Tab1:** Schedule of screening, data collection, and outcomes assessments for the ED-AWARENESS-2 Trial

Measurement/event	ED	Extubation	^a^1	2	3	4	5	6	7	MV^b^	HOSP D/C	Day 30	Day 180
Inclusion criteria	X												
Exclusion criteria		X											
Demographics, baseline data	X												
Laboratory values	X												
Blood gas values	X		X										
ED procedures and care	X												
Intubation meds and location	X												
Safety events (i.e., intubation success, unplanned extubation, cardiac arrhythmia, allergy, MH)	X												
Ventilator settings/data	X												
Sedation depth (RASS, SAS), documented by bedside nurse	X		X	X	X	X	X	X	X				
Medications for sedation, analgesia, NMB	X		X										
Delirium assessment/CAM-ICU			X	X	X	X	X	X	X				
Assessment of AWP		X											
Ventilator duration										X	X		
Length of stay (hospital and ICU)											X		
Discharge location											X		
Mortality status											X		
Mental health and QOL assessments												X	X

*ED* emergency department; *MV* mechanical ventilation; *MH* malignant hyperthermia; *RASS* Richmond Agitation-Sedation Scale; *SAS* Sedation-Agitation Scale; *NMB* neuromuscular blockade; *CAM* confusion assessment method; *ICU* intensive care unit; *QOL* quality of life

^a^The numbers 1–7 refer to hospital days, with hospital day 1 referring to the first day after admission from the ED

^b^If patient is extubated for 24 h or more, then that is the end of ventilation duration. If patient is extubated and re-intubated within 24 h, this is treated as though they were never extubated

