**Fig. 2 Fig2:**

Example novel paradigm and hypothesized causal pathway for improving patient-centered outcomes. It is possible that by addressing the early period of critical illness in the emergency department, modifiable targets (increasing provider compassion, decreased patient-perceived threat, preventing awareness with paralysis) can be used to improve patient-centered clinical outcomes

There is significant rationale to target rocuronium use in the ED as a means to prevent AWP. In the ED-AWARENESS Study and ED-SED Pilot Trial, 19/23 (92.6%) AWP patients received rocuronium [19, 23]. In multivariable analysis, rocuronium was independently associated with AWP (adjusted odds ratio, 6.05; 95% CI, 1.46–17.56) [19, 23]. Importantly, AWP was not associated with other sedation-related variables, including (1) sedation monitoring; (2) analgesics, sedatives; or (3) sedation depth. This confirms that a proposal to target ED-based rocuronium may have the greatest chance to improve safety and prevent AWP. This is critical as data from the National Emergency Airway Registry (*n* = 17,583) show rocuronium use was 5% for intubations in 2002, yet up to ~ 45% by 2012 [14]. Use was up to 49% in our ED SED Study, and 60% in the ED-SED Pilot Trial [17, 21]. This indicates that AWP is likely a growing health problem. Contrary to a 5-min duration of succinylcholine (the historical default NMB), rocuronium can paralyze for up to 150 min, greatly increasing AWP risk. In addition, in clinical trials comparing rocuronium versus succinylcholine, with respect to intubating conditions, data has either favored succinylcholine or shown no difference in outcomes [43–45]. However, other preliminary work from our research team did not show an association between rocuronium and AWP risk, but rather pre-intubation mental status [24]. This suggests equipoise in the data and further confirms the need for this large-scale clinical trial.

Our objective is to conduct a pragmatic clinical trial aimed at limiting rocuronium exposure in order to reduce the proportion of mechanically ventilated ED patients experiencing AWP. We hypothesize that limiting rocuronium exposure in the ED, using succinylcholine as the default NMB of choice, will significantly reduce the proportion of patients experiencing AWP.

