### Safety monitoring

A data and safety monitoring board (DSMB), independent of the research team and sponsor, will be used to monitor the data. The DSMB will assess safety and efficacy of trial procedures and monitor the overall conduct of the trial. The DSMB also will review adverse event data, other safety data, quality and completeness of data, protocol adherence data, and enrollment data at each meeting to ensure proper trial conduct and continued feasibility of answering the research questions. Meetings between the research team and the DSMB will occur before the study begins, after 25% of the total sample size is accrued each time, and upon trial completion.

The intervention is designed to enhance patient safety by quality improvement related to the selection of neuromuscular blockers by clinicians. Consequently, we aim to see an increase in succinylcholine use during the intervention phase of the trial, which is congruent to clinical practice for more than 40 years and consistent with recommendations for preventing awareness with paralysis. There is over a decade of research on tens of thousands of patients showing equivalent intubation success rates between succinylcholine and rocuronium. In addition, intubation success rate in the ED approaches 100% [14, 54]. We therefore, do not expect to see any difference in intubation success rate between the control and intervention phases, but will track and report this measure. Given the typically small and transient increase in serum potassium of ~ 0.5 to 1 mEq/L known to occur with succinylcholine, there is the potential for an increase in cardiac arrhythmias related to hyperkalemia to occur in the intervention phase. The overall incidence of cardiac dysrhythmia in the peri-intubation period in the ED is approximately 0.7% with no difference between succinylcholine and rocuronium. We therefore do not expect to see any difference in this adverse event between the control and intervention phases, but will track and report this measure [14]. Other very rare adverse events associated with succinylcholine include malignant hyperthermia (incidence ~ 0.009%) and allergic reaction to succinylcholine (incidence 0.01%) [73, 74]. Both of these adverse events are quite unlikely to occur, but will be tracked and reported. Unexpected events will be reported by the site principle investigators to the CCC as detected.

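### Unplanned extubation is scheduled for capture in the ED only, so a phase comparison can partly reflect when paralysis wears off rather than how many patients are harmed

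*Protocol article*

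**What the plan says.** In the Data section, Table 1 has a row reading "Safety events (i.e., intubation success, unplanned extubation, cardiac arrhythmia, allergy, MH" with one mark, under ED. Nothing is marked under extubation, hospital days 1 to 7, mechanical ventilation or hospital discharge. Other rows do run on: "Sedation depth (RASS, SAS), documented by bedside nurse" is marked in the ED and on days 1 to 7, delirium on days 1 to 7, and medications including the neuromuscular blocker (NMB) in the ED and on day 1.

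Safety monitoring undertakes to track and report intubation success and arrhythmia, and says of malignant hyperthermia and allergy: "Both of these adverse events are quite unlikely to occur, but will be tracked and reported". It does not mention unplanned extubation, which appears only in the Table 1 row. The same section has site investigators report unexpected events as they are detected, and sends adverse and serious adverse events to each DSMB meeting, with no ED limit on either. It adds that the adverse event review process applies to sites only after their transition to the intervention.

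On duration of action, the Background states: "Contrary to a 5-min duration of succinylcholine (the historical default NMB), rocuronium can paralyze for up to 150 min". It also says that patients given an NMB cannot move.

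**The concern.** Self-extubation requires movement, so a patient becomes at risk only as paralysis wears off. The trial's purpose is to move patients from a longer-acting to a shorter-acting agent. With capture scheduled only in the ED, the agent helps to decide whether a given extubation falls before the patient leaves, and is counted, or after, and is not. Two phases with nearly the same risk over a fixed period from dosing could then show different ED counts, with the excess in the intervention phase.

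At stake is how one listed safety measure is read. A DSMB member or a reader of the results could take a higher ED count as more patients harmed under the succinylcholine default, when part of it may be events moved across the ED boundary. An ED-only count cannot separate the two.

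**Working it through.** The article gives no unplanned-extubation rate, time at risk or ED length of stay, so there is no stated figure to reproduce. The calculation below is illustrative.

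**Inputs from the article**
- Duration of paralysis: 5 min (succinylcholine) and up to 150 min (rocuronium), from the Background. The second figure is a maximum.
- Rocuronium use in earlier studies: "Use was up to 49% in our ED SED Study, and 60% in the ED-SED Pilot Trial". The figures 49% and 60% serve as a proxy for the control phase.

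**Assumptions**
- Rocuronium use in the intervention phase: 10% to 30%. No figure is given, and clinicians remain free to choose ("the final choice of all treatment decisions will remain at the discretion of the treating clinical team at all times").
- ED stay after the dose, L: 1 to 12 h, the same in both phases.
- One dose per patient, with every rocuronium dose lasting the full 150 min in the main table.

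**Formula**
- Unparalysed ED minutes: S = L − 5 after succinylcholine; R = max(L − 150, 0) after rocuronium.
- Phase mean with rocuronium share r: r × R + (1 − r) × S.
- Ratio: intervention mean ÷ control mean.

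**Worked examples**
- L = 150 min, 60% vs 10%: S = 145, R = 0. Control 0.4 × 145 = 58.0; intervention 0.9 × 145 = 130.5; ratio 2.25.
- L = 240 min, 60% vs 10%: S = 235, R = 90. Control 54 + 94 = 148; intervention 9 + 211.5 = 220.5; ratio 1.49.
- L = 720 min, 49% vs 30%: S = 715, R = 570. Control 279.3 + 364.65 = 643.95; intervention 171 + 500.5 = 671.5; ratio 1.04.

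| ED stay after dose | 60% vs 10% | 49% vs 30% |
|---|---|---|
| 1 h to 150 min | 2.25 | 1.37 |
| 4 h | 1.49 | 1.17 |
| 6 h | 1.27 | 1.10 |
| 8 h | 1.19 | 1.07 |
| 12 h | 1.12 | 1.04 |

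**Sensitivity to duration.** If rocuronium lasts 60 min (an assumption), the 60% vs 10% ratio is 1.34 at 2 h, 1.14 at 4 h and 1.06 at 8 h.

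**Fixed 24 h window from the dose.** S = 1435, R = 1290, assuming equal ventilated time in both phases.
- 60% vs 10%: control 774 + 574 = 1348; intervention 129 + 1291.5 = 1420.5; ratio 1.05.
- 49% vs 30%: control 632.1 + 731.85 = 1363.95; intervention 387 + 1004.5 = 1391.5; ratio 1.02.

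These are ratios of unparalysed time. They become ratios of event counts only if the hazard of self-extubation is constant once paralysis ends, which the article gives no means of checking.

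**Does the adverse event text fill the gap?** Unplanned extubation is a listed event, so the route for unexpected events does not clearly cover it. The adverse event review applies only after transition, so it cannot supply a control-phase count. The Table 1 row is the only stated capture that serves both phases, and it is marked for the ED alone.

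**The case against.** The strongest reply is that there is no bias. One rule, the ED stay, sets the window in both phases. Shorter paralysis is what the intervention is meant to produce, so extra extubations in the ED would be a real effect of drug choice on ED harm. Dividing by unparalysed time would adjust away part of that effect. This stands: the ED count is a true ED count, and the article never says it will be read as risk over the whole stay. What remains is narrower. Safety monitoring looks at safety measures by phase, and a reader will naturally take the result as harm to patients.

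A reader might also infer more than the article supports:
- **That the phases differ by 5 versus 150 minutes.** That is a contrast between drugs, at one drug's maximum. Both phases mix the two agents.
- **That safety events are recorded nowhere but the ED.** They are scheduled only there. Unexpected events and adverse events have reporting routes with no ED limit.
- **That late allergy, malignant hyperthermia or arrhythmia is materially lost.** At the stated 0.009% and 0.01%, even 3090 patients all given succinylcholine would yield 3090 × 0.00009 = 0.28 and 3090 × 0.0001 = 0.31 expected events. For arrhythmia, the article's background rate is itself tied to the ED: "The overall incidence of cardiac dysrhythmia in the peri-intubation period in the ED is approximately 0.7% with no difference between succinylcholine and rocuronium". The ED mark matches that frame.

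It is also fair that no hypothesis, test or stopping rule depends on unplanned extubation, and that an article may leave exact event windows to the full protocol. But Table 1 does not leave this one open: it places the row in the ED column.

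**Conclusion.** The point holds in a limited form. Unplanned extubation is scheduled for the ED only, and an excess in the intervention phase could partly reflect extubations after rocuronium that occur once the patient has left. The count would be correct for the ED and potentially misleading as a statement of harm per patient. It should not be called a biased comparison.

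The direction is the same in every scenario run, but the size is not established. At a 150-minute effect the phase-level ratio of unparalysed ED time is about 1.04 to 2.25, depending on assumed ED stay and intervention-phase rocuronium use. The top value needs stays of 150 minutes or less, every dose lasting the stated maximum and a switch from 60% to 10%. Shorter rocuronium action brings the ratio closer to 1. A 24-hour window reduces it to about 1.02 to 1.05 under the same assumptions. This is an inexpensive improvement to a secondary safety measure and does not touch the primary analysis.

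**What to change.** Capture unplanned extubation over one fixed clock window from the first NMB dose in the ED, for example 24 hours, the same in both phases and at all sites. Report it by phase beside the ED count, so that a reader can see whether an ED difference persists over the fixed window. The window should be counted in hours from the dose and not end at hospital day 1: the first Table 1 footnote defines that day from admission out of the ED, so such an endpoint would still move with time spent there.

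Reconcile Table 1 with Safety monitoring: state which listed events are captured in both phases and until when, and how that relates to an adverse event review that starts only after transition.

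The cost is a changed Table 1 row and one more chart-abstraction field. The drawback is that some ICU extubations unrelated to NMB choice will be added in both phases, which is one reason to keep the ED count alongside.
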